# A multi-center, randomized, parallel-group study to compare the efficacy of enhanced cognitive behavior therapy (CBT-E) with treatment as usual (TAU) for anorexia nervosa: study protocol

**DOI:** 10.1186/s13030-023-00277-2

**Published:** 2023-05-29

**Keywords:** Adolescent, Adult, Anorexia nervosa, Feeding and eating disorders, Psychological treatments, Randomized controlled trial, Enhanced cognitive behavioral therapy

## Abstract

**Background:**

The superiority of Enhanced Cognitive Behavior Therapy (CBT-E) with regard to weight gain and improvement of psychopathology of eating disorders for patients with anorexia nervosa (AN) over other psychotherapies and treatment as usual (TAU) has not been demonstrated in randomized controlled trials (RCTs). However, a previous RCT showed that patients with AN whose baseline body mass index (BMI) was less than 17.5 kg/m^2^ gained more weight when treated with CBT-E than with other psychotherapies. The aim of the study is to compare the efficacy of CBT-E and TAU for patients with AN. It was hypothesized that CBT-E would be superior to TAU, at least in terms of weight gain, as most patients with AN are likely to have a BMI lower than 17.5 kg/m^2^.

**Methods/design:**

A randomized parallel-group multicenter trial will be conducted in three teaching hospitals in Japan between January 2023 and March 2026. Patients with DSM-5 AN, aged 16 years and older, with a BMI equal to or above 14.0 and below 18.5 will be eligible to participate. 56 patients will be randomly and evenly assigned to two intervention groups (CBT-E and TAU). Those assigned to CBT-E will be offered 25–40 sessions in accordance with their initial BMI. Patients assigned to TAU will have at least one session every 2 weeks, with the number of sessions and treatment period not fixed in advance. The primary outcome is BMI at 40 weeks after treatment initiation. The secondary outcomes are the results from the Japanese version of the Eating Disorder Examination Questionnaire and Clinical Impairment Assessment questionnaire to measure eating disorder psychopathology and psychological impairment. The follow-up assessment will be performed 6 months after the 40-week assessment.

**Discussion:**

This multi-center randomized controlled study will probably evaluate the efficacy of CBT-E compared with TAU for patients with more severe AN than in previous studies since Japanese patients are likely to have a lower BMI than those in Western countries. While it may be difficult to generalize the results of a study conducted in Japan, it would be valuable to clarify the efficacy of CBT-E as a treatment package.

**Trial registration:**

UMIN, UMIN000048847. Registered 12 Sep 2022.

**Supplementary Information:**

The online version contains supplementary material available at 10.1186/s13030-023-00277-2.

## Background

Anorexia nervosa (AN) is a serious psychiatric disorder characterized by intense fear of weight gain, abnormal eating, and disturbed body image and body weight [1]. Psychotherapeutic interventions are the first-line treatment. Several treatment guidelines, such as the Clinical Practice Guidelines of the Royal Australian and New Zealand College of Psychiatrists, the Dutch Practice Guideline for the Treatment of Eating Disorders, and the UK National Institute for Health and Care Excellence Clinical Guidelines for Eating Disorders (NICE guidelines) recommend eating disorder focused cognitive behavior therapy (CBT) for eating disorders (EDs). Enhanced Cognitive Behavior Therapy (CBT-E) is the form of CBT with the strongest evidence base and, as such, is a, treatment of choice for AN [2–4]. Nevertheless, only limited research has provided support for CBT-E for adult and adolescent patients with AN.

For patients with bulimia nervosa (BN) or binge eating disorder (BED), evidence that CBT-E is more effective in terms of improving alleviating eating disorder features and general psychopathology than other treatments has been accumulating [5–8].

For patients with AN, cohort studies have shown that CBT-E is effective both for adult and adolescent patients with AN. A cohort study of adult patients with AN demonstrated a substantial increase in weight and marked improvement in ED symptoms in those patients who completed outpatient CBT-E treatment [9]. In adolescent patients with AN receiving outpatient CBT-E, eating disorder and general psychopathology improved to a similar degree as with adult patients by the end of treatment with both considerable weight gain and reduced scores for clinical impairment, eating disorder, and general psychopathology at the end of treatment and also at 20-week follow-up [10, 11] .

Network meta-analysis suggests that CBT-E may be superior to both the Maudsley Anorexia Nervosa Treatment for Adults (MANTRA) and Specialist Supportive Clinical Management (SSCM) recommended by the NICE guideline [4] in terms of weight restoration, though confidence in the evidence was low due to heterogeneity or inconsistency between studies [12].

Despite these positive findings favoring CBT-E, some studies have failed to find that it is superior to other active psychological treatments. The Anorexia Nervosa Treatment of OutPatient (ANTOP) study compared the efficacy of two manual-based outpatient treatments for AN: focal psychodynamic therapy, CBT-E, and treatment as usual (TAU) and showed that there were no significant differences in weight gain between any of these treatments [13]. The Strong Without Anorexia Nervosa (SWAN) study, an RCT that compared three psychological treatments for AN (MANTRA, SSCM, and CBT-E) in outpatient settings also failed to show that there were significant differences in weight regain, improvement in ED psychopathology, and psychosocial impairments between these treatments [14].

Although the superiority of CBT-E over other therapies has not been demonstrated in RCTs, subgroup analysis of patients with a baseline BMI less than 17.5 kg/m^2^ in the ANTOP study revealed that mean BMI at the end of treatment was significantly higher in those who received CBT-E than in those who received focal psychodynamic therapy [13]. A similar finding was obtained in the previously mentioned cohort study [9]. These results suggest that the CBT-E may differentially be effective in those with AN and a low BMI. In Japan, most patients diagnosed with AN have a BMI lower than 17.5 kg/m^2,^ and therefore the study might provide the opportunity to investigate the possibility that CBT-E is more efficacious for patients with AN and with lower BMIs than other active treatments both in terms of weight gain and improvement in ED psychopathology. Previous RCTs have included patients with AN diagnosed by DSM-IV criteria, while this study will employ DSM-5 criteria, providing the opportunity to investigate outcome in this group.

## Objectives and hypotheses

The aim of this study is to compare the efficacy of CBT-E with TAU for patients with AN in a RCT. It is hypothesized that CBT-E will be superior to TAU, in terms of weight gain, especially in Japan as most patients with AN are likely to have a BMI less than 17.5 kg/m^2^.

## Methods

### Trial design

This is a multicenter study, stratified by trial sites (The University of Tokyo Hospital, Kohnodai Hospital, and Kyushu University Hospital) and BMI (below 16.0, above or equal to 16.0 and below or equal to 17.5, and above 17.5 and below 18.5), using dynamic balanced randomization and a no-blind, parallel-group design that will be conducted in Japan [15]. Figure 1 shows the flow diagram of participants through the trial.

**Fig. 1 Fig1:**
[figure not shown]
Flow diagram of the participants. *CBT-E*: Enhanced cognitive behavioral therapy, *TAU*: treatment as usual. *T0*: baseline, *T1*: week 20, *T2*: end of treatment, week 40, *T3*: follow-up, 6 months after *T3*. *SCID-5 RV*: Structured Clinical Interview for DSM-5 Disorders, Research Version, *EDE-Q*: The Eating Disorder Examination Questionnaire, *CIA*: Clinical Impairment Assessment questionnaire. The number and frequency of sessions of CBT-E vary according to baseline BMI shown in the Supplementary Table S1. The treatment period and intensity of the TAU are not specifically determined in advance. When participants are remitted at the interim assessment (*T1*), the study treatment will be terminated. Remission was defined as BMI ≥ 18.5 and the EDE-Q-J global score below 1 stand deviation above the community mean

### Participants

The present study will recruit 56 participants. The University of Tokyo Hospital will recruit 23 patients, Kohnodai Hospital 10 patients, and Kyushu University Hospital 23 patients. The participants will be recruited via online advertisements through official websites and advertisements on hospital bulletin boards. Patients referred from another medical facility with suspected AN will also be recruited at their first visit. To be eligible to participate in this study, participants must meet all the inclusion and exclusion criteria listed in Table 1.

**Table 1 Tab1:** Eligibility criteria for participants

Inclusion criteria	• Those who meet the criteria of DSM-5 for AN. • Those who are 16 years old or older when they give consent to participate in the study. • Those whose BMI are equal to or above 14.0 and below 18.5. • Those living in Japan who are literate in Japanese. • Those who understand the study concepts and give written informed consent.
Exclusion criteria	• Those who are receiving or have received any type of structured psychotherapies including CBT-E, Family therapy, Maudsley Model of Anorexia Nervosa Treatment for Adults (MANTRA), Specialist Supportive Clinical Management (SSCM), Interpersonal Therapy (IPT) within the last year. • Those who have mental illnesses* including schizophrenia, bipolar disorder or substance use disorder, or somatic disease that impedes the study treatment. • Those who are currently receiving antipsychotic medication except for antidepressants, anxiolytics, or hypnotics (The participants on antidepressants or hypnotics will not be excluded as far as they are on stable or reducing dose during the study). • Those who have an intellectual disability. • Those who have suicidal ideation. • Those who are pregnant or might become pregnant. • Those who have difficulty in attending therapy on schedule. • Those whom therapists or physicians consider as ineligible to participate in this study.

*: The Structured Clinical Interview for DSM-5, Research Version (SCID-5-RV), is used to exclude patients with any history of schizophrenia, bipolar disorder, or substance use disorder

### Settings and locations

The study will be carried out at The University of Tokyo Hospital, Kohnodai Hospital, National Center for Global Health and Medicine, and Kyushu University Hospital between 2023 and 2026. The University of Tokyo Hospital is one of the largest tertiary care teaching hospitals with more than 1,200 beds located in Tokyo, the political and economic center of Japan, with a population of approximately 14 million. Kohnodai Hospital is a secondary care hospital with approximately 300 beds in Ichikawa, a city located within 10 to 20 km from the center of Tokyo, with a population of approximately 500,000. Kyushu University Hospital is also one of the largest tertiary care teaching hospitals with more than 1,200 beds located in Fukuoka, the sixth-largest city in Japan, with a population of approximately 1.6 million.

### Interventions

Participants will be randomly assigned to receive either CBT-E or TAU. They will not be allowed to receive any other psychotherapy except the treatment they are assigned during the treatment and follow-up period. CBT-E and TAU will be provided in outpatient settings by different therapists, who have had more than 2 years of experience in treating patients with EDs. The assignment of therapists will be carried out in a manner that there is not substantial difference in years of experience in treating EDs between the two treatment therapists. CBT-E will be offered only by physicians or psychotherapists who have been supervised or are currently being supervised by [name], who is one of the most prominent international CBT-E specialists. When the treatment sessions are conducted by psychotherapists, the attending physician monitors the participants’ physical conditions before or after each session. If their BMI falls below 14 or any medical instability emerges, treatment will be suspended for up to 3 weeks for inpatient treatment or corresponding treatment to address the condition. The BMI of 14 was considered the lower cutoff limit in previous studies and in the guidelines of Japan Society for Eating Disorders [13, 14, 16]. If the patient does not recover within 3 weeks, they will be withdrawn from the study. If participants are remitted at 20 weeks after treatment initiation, the treatment will be terminated. Remission will be defined with reference to previous studies: a BMI ≥ 18.5 and an EDE-Q-J global score less than 1 SD above the community mean [6, 8, 17, 18].

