### Sample size

To detect an effect size of 0.96 in BMI increase estimated in previous studies, with a two-sided 5% significance level and power of 80%, a sample size of 28 patients per group was deemed necessary, given an anticipated drop rate of 30% [13, 14]. A 24-month enrollment period is needed to recruit this number of patients. The number of participants recruited at each site is as follows: The University of Tokyo Hospital will recruit 23 patients, Kohnodai Hospital 10 patients, and Kyushu University Hospital 23 patients.

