### Randomization

The generation and implementation of the centralized randomization sequence will be conducted independently from the trial teams using the cloud version of UMIN Internet Data and Information system for Clinical and Epidemiological research (cloud INDICE). Participants are randomly assigned to one of the two trial arms in a 1:1 ratio, using a computer-generated, dynamic procedure (minimization) stratified by trial sites and BMI (below 16, above or equal to 16 and below or equal to 17.5, and above 17.5 and below 18.5). Participants will be allocated, with an 80% probability, to the group that minimizes between-group differences in BMI and trial site among all participants. Whereas patients, psychotherapists, and physicians are aware of which group they belong to, outcome assessors and data analysts will be kept blinded to the allocation.

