### Statistical methods

The primary outcome is a BMI at 40 weeks after treatment in the intention-to-treat population. The secondary outcomes are eating disorder psychopathology and impairment measured by EDE-Q-J and CIA questionnaires. Multilevel modeling will be applied to longitudinal analyses of BMI and scores on the EDE-Q-J and the CIA of patients nested within hospitals.

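### Therapists are nested within arm but the stated model clusters only by hospital, so the type I error of the week-40 BMI contrast may exceed 5%

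*Protocol article*

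**What the plan says.** Under Interventions, the protocol article states that "CBT-E and TAU will be provided in outpatient settings by different therapists". It requires more than two years' experience with eating disorders and asks that years of experience be similar between the two sets of therapists. CBT-E therapists are also, or have been, supervised by one specialist.

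Under Statistical methods, the only clustering named is by hospital: "Multilevel modeling will be applied to longitudinal analyses of BMI and scores on the EDE-Q-J and the CIA of patients nested within hospitals".

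Under Sample size, the target is an effect size of 0.96 "with a two-sided 5% significance level and power of 80" per cent; "a sample size of 28 patients per group was deemed necessary, given an anticipated drop rate of 30" per cent. No allowance for clustering is mentioned.

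Under Randomization, "Participants are randomly assigned to one of the two trial arms in a 1:1 ratio", by minimization on site and BMI. The article gives no number of therapists and no ICC.

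**The concern.** Randomization is of individual patients, but treatment is delivered in therapist-sized groups that lie wholly inside one arm. Patients of one therapist may do better or worse together. That shared component does not cancel between arms, because no therapist has patients in both.

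The hospital level behaves differently. Each hospital is expected to contribute patients to both arms, so a hospital effect largely drops out of the treatment contrast. The level that the article names therefore does little for the primary comparison, and the level that it does not name falls directly on it.

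At stake is the precision claimed for the week-40 BMI difference. If therapist variance is positive and ignored, the standard error is too small, the confidence interval too narrow and the nominal 5% test too liberal. With few therapists per arm, one or two unusually effective or ineffective ones could carry the result.

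**Working it through.** **1. The stated sample size.** Inputs from Sample size: standardised effect 0.96, two-sided 5%, power 80%, dropout 30%. A two-sample t-test (non-central t) needs 18.05 evaluable per arm, so 19. Then 19 / 0.70 = 27.1, rounded up to 28. The stated figure reproduces exactly with no design effect. With 28 recruited per arm, 28 × 0.70 = 19.6, so about 20 are evaluable, and power with independent patients is 84%.

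**2. Assumptions.** Neither therapist numbers nor the ICC is given. I take one, two or three therapists per arm per hospital (3, 6 or 9 per arm) and therapist ICCs of 0.02, 0.05 and 0.10, with 0 as reference.

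**3. Type I error when therapist is ignored.** Simulation under no treatment effect: hospitals in the planned 23/10/23 proportions, 70% evaluable (about 39 patients), therapists nested in arm within hospital, analysis by arm plus fixed hospital.

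| Therapists per arm per hospital | ICC 0.02 | ICC 0.05 | ICC 0.10 |
|---|---|---|---|
| 1 | about 6.2–6.6% | about 9% | about 13% |
| 2 | about 5.6% | about 6.8% | about 8% |
| 3 | about 5.5% | about 6% | about 7% |

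At ICC 0 the rate is about 5%, as it should be. Repeat runs differ by a few tenths of a point. The mean estimated treatment effect under the null stays at about zero throughout, so the fault lies in the standard error and not in the estimate.

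A formula check: design effect DE = 1 + (m − 1) × ICC, with m evaluable patients per therapist, and true type I error ≈ 2 × [1 − Φ(1.96 / √DE)].
- One therapist: m = 20/3 = 6.67. At ICC 0.05, DE = 1 + 5.67 × 0.05 = 1.28, giving about 8.4%. The simulated 9% is slightly higher, as expected with unequal hospital sizes.
- Two therapists: m = 20/6 = 3.33. At ICC 0.02, DE = 1.047, giving about 5.5%.

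If all 28 per arm contribute, clusters are larger and so is the excess: with one therapist per arm per hospital, 11.1% at ICC 0.05 and 17.2% at ICC 0.10.

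**4. Power with a corrected standard error.** With 20 evaluable per arm and ICC 0.05, replace 0.96 by 0.96 / √DE.
- Two therapists per arm per hospital: DE = 1 + 2.33 × 0.05 = 1.12, power about 80%.
- One therapist: DE = 1.28, power about 74%.

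Both keep 38 patient-level degrees of freedom (20 + 20 − 2). A model with a therapist random intercept and small-sample degrees of freedom may have far fewer. With one therapist per arm per hospital there are 6 therapists: 6 − 2 = 4 degrees of freedom for arm alone, or 6 − 4 = 2 with hospital fixed as well. The same non-central t then gives about 53% (4 df) or 33% (2 df). With two per arm per hospital (12 therapists, 8 to 10 df) it gives about 71 to 74%. These are limiting cases, since the actual degrees of freedom depend on the estimated variances.

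**The case against.** The strongest reply is that the size of the problem is unknown. The documents give no therapist count and no ICC, and nothing in them supports 0.05 or 0.10 for BMI in particular. With three therapists per arm per hospital and an ICC of 0.01, type I error is 5.1%. The experience requirement, the balancing of experience and the shared CBT-E supervision plausibly reduce therapist variance. All of this stands, and the point has to be stated conditionally. It does not remove the point: balancing mean experience does not remove correlation among patients of the same therapist, and the article's Discussion itself expects therapists to differ in experience and leaves the content of TAU loosely prescribed.

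A second reply is that one sentence in a condensed article does not exclude a therapist level or a hospital-by-arm effect in a fuller plan. That is fair. But the article does state a nesting structure, and the one it states does not match how treatment is delivered.

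A third reply is that a therapist variance estimated from very few therapists is unreliable and costs many degrees of freedom. This also stands. It makes a mandatory therapist term in the primary model debatable.

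A reader might infer more: that therapist differences bias the treatment estimate, that the error rate certainly exceeds 5%, or that therapist identity is not being recorded. The documents support none of these. The estimate is unbiased on average over therapists, the excess vanishes at ICC 0, and the article does not say what is recorded.

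**Conclusion.** The point holds in conditional form. The article fixes separate therapists for each arm, names clustering by hospital only, and sizes the trial as if patients were independent. For any positive therapist ICC, with more than one patient per therapist, the standard error of the week-40 BMI contrast is too small.

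The size depends on two assumed inputs. It runs from negligible, with many therapists and an ICC near 0.01, to a true error rate of about 13% with one therapist per arm per hospital and an ICC of 0.10 among those evaluable. The stated power is similarly optimistic if therapists are few. This is a cheap improvement to the plan, not a flaw that undermines the trial.

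**What to change.** 1. Ensure that therapist identity is in the analysis dataset for every patient.
2. Pre-specify an analysis of the primary contrast with a random intercept for therapist, nested in arm within hospital, with small-sample degrees of freedom. At minimum, make it a sensitivity analysis.
3. Where a hospital has only one or very few therapists per arm, report the contrast with standard errors under assumed therapist ICCs of 0, 0.05 and 0.10.
4. Add to the sample-size text that the 80% power assumes no therapist clustering.

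The cost is at most one data field, one additional analysis and one sentence. The downside is a wider confidence interval in that analysis, possibly considerably wider when therapists are few, and a less favourable power statement.

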#### CBT-E

CBT-E is a treatment for the full range of ED presentations, irrespective of ED diagnosis. With patients who are underweight, CBT-E has three phases [19]. In the first phase, the emphasis is on increasing patients’ motivation to change and helping them recognize their current maladaptive thinking and behaviors and the processes maintaining them. Initially, patients are encouraged to commence and maintain self-monitoring (one of the crucial factors in CBT-E), adopt a regular pattern of eating, and actively make the decision to address weight restoration. Subsequently the treatment is focused on continuing to address weight restoration and eating disorder psychopathology, such as extreme concerns about their shape and weight. Patients are encouraged to gain weight until their BMI falls within the normal range (18.5–24.9 kg/m^2^). In the final phase, the focus is on helping patients maintain the changes that they have achieved and developing strategies in advance for risky situations that might trigger setbacks. Patients assigned to CBT-E are offered 25–40 sessions that last about 50 min over a 40-week period. The focused form of CBT-E will be offered and the number of sessions varies according to the participants’ BMI at their first visit (below 16: 40 sessions, above or equal to 16 and below or equal to 17.5: 30 sessions, above 17.5 and below 18.5: 25 sessions) to allow for enough time to regain weight, following the protocol devised for the SWAN study [14]. The detailed information about the schedule and frequency of sessions is shown in the Supplementary Table S1.

